**Fig. 1 Fig1:**
[figure not shown]
EPaL study design

### Ethical approval

The study was approved by the Medical Research Ethics Committee of the Faculty of Medicine and Health Sciences at Universiti Putra Malaysia, Selangor, Malaysia. Permission for field data collection in secondary schools was attained from the Malaysian Ministry of Education, as well as the State Department of Education of Selangor. In all cases, consent was obtained from the board of the school, the principal, the parents and the adolescents prior to data collection.

### Setting, recruitment and participants

Two schools were randomly selected in the district of Hulu Langat, the state of Selangor, Malaysia. One school will randomly chose to receive the intervention, while adolescents in the other served as the comparison group. Selection of the schools will be performed by means of a draw from a list of schools in Selangor, obtained from the website of the state’s Department of Education. Only schools that met the inclusion criteria (coeducational, multiracial, non-residential and non-religious) were included in the draw. Adolescents who were Form 1 or 2 students and 13–14 years old; and whose parents consented to the intervention met the criteria for inclusion in the study.

A seminar will be held for the parents and teachers of Form 1 and 2 students in which EPaL will be introduced. Parents and teachers were asked to promote the programme to the students. Recruited students were presented with the research’s information sheet and consent letters to be read and filled by them and their parents. Written consent letters were collected from participating adolescents and their parents prior to the intervention. Thereafter, the students were subjected to the EPaL intervention programme over the course of 16 weeks in their school. They were assessed in three points of assessments, which are prior to the intervention (baseline), after the final session of the programme (post-intervention) and 3 months thereafter (follow-up).

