## Methods/Design

### Study design

EPaL is a school-based intervention programme targeting adolescents in the early years of secondary school. The present study adopted a quasi-experimental design, in which adolescents from one school were included in the intervention group, while those from another school served as the comparison group and were not subjected to the intervention until the end of the period of experimentation. Adolescents in the comparison group attended a standard physical and health education class at least once a week. As the study was concluded, they were allowed to receive EPaL modules and educational materials. A flowchart of the intervention is shown in Fig. 1.

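### Eligibility rests on parental consent to the intervention, and the only recruitment route described leads into EPaL, so the two schools may enrol differently motivated students

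*Protocol article*

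**What the plan says.** All references are to the protocol article.

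- **Allocation** (Setting, recruitment and participants). "Two schools were randomly selected in the district of Hulu Langat", and then "One school will randomly chose to receive the intervention, while adolescents in the other served as the comparison group". The date of this draw relative to student enrolment is not given.
- **Eligibility** (same section). Form 1 or 2 students aged 13–14 "whose parents consented to the intervention met the criteria for inclusion in the study". It is written once, for the whole study.
- **Recruitment** (same section). It opens with an information event, at which the programme is presented to families and staff. Beyond that event, "Parents and teachers were asked to promote the programme to the students". Students and parents then sign consent letters. "Thereafter, the students were subjected to the EPaL intervention programme over the course of 16 weeks in their school".
- **Comparison school** (Study design). Its students "were not subjected to the intervention until the end of the period of experimentation". They keep their usual physical and health education class, and may have the EPaL modules and materials once the study is over.
- **Consent** (Ethical approval). It was obtained from school, parents and adolescents in every case before data collection.
- **Analysis** (Data analysis). A t-test, chi-square and repeated measures ANOVA are named, with evaluation by intention to treat. No adjustment for baseline differences is named.
- **Limitations** (Discussion). The authors concede that randomisation applied only to the schools. Selective enrolment by arm is not mentioned.

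**The concern.** A criterion worded as consent to the intervention has a plain meaning in the EPaL school: the family agrees that the child joins a club running eight sessions over 16 weeks. In the comparison school the same words can refer only to assessments now and EPaL materials after the study. If families know their school's role when they sign, one rule asks for two different commitments, and different students may pass it.

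Willingness to join a healthy-lifestyle programme is plausibly related to what the trial measures: stages of change, eating and activity behaviour, body image, and knowledge, attitude and practice. A difference between schools after the programme could then partly reflect who signed up. Intention-to-treat analysis does not help, because the selection happens before entry. The problem is also distinct from having one school per arm, since differential enrolment would bias the comparison even with many schools.

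**Working it through.** **1. What the text establishes and what it leaves open**

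| Question | What the article gives |
|---|---|
| Consent to what? | To the intervention, for the whole study |
| Recruitment route | A seminar introducing EPaL, then promotion; the school or schools are not named |
| What follows consent | The 16-week EPaL programme, so the route as written fits the intervention school |
| What comparison parents agreed to | Not stated |
| Role draw before or after enrolment | Not stated; it comes first in the order of the text |
| Roles undisclosed at consent | Not stated |

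The eligibility rule and the recruitment route are stated. The sequence and the comparison school's procedure are not.

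**2. The plan's own figure**

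The Sample size calculation gives 40.3% and 27.9% (a gap of 12.4 points), 80% power, 5% significance and 234 per group. Taking the test as two-sided:

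- Arcsine difference: h = 2·arcsin(√0.403) − 2·arcsin(√0.279) = 0.2626.
- n = 2 × ((1.960 + 0.842) / 0.2626)² = 228 per group. The pooled two-proportion formula gives 229.
- Both are within 3% of 234, and power at 234 is 0.81. The figure is reproduced closely enough to use 234 below.

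**3. Illustration of what an imbalance would do (assumed inputs)**

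The article gives neither uptake nor any difference between willing and unwilling students. Assume that each school has the same overall prevalence, and that enrolled and non-enrolled students differ by d points in both. The arms then differ, with no EPaL effect, by

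imbalance = (comparison uptake − EPaL uptake) × d.

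The standard error of the difference at an assumed 30% prevalence is √(2 × 0.30 × 0.70 / 234) = 4.24 points. The two-sided rejection rate is P(Z > 1.96 − imbalance/4.24) + P(Z < −1.96 − imbalance/4.24).

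| Assumed uptake, comparison / EPaL | Assumed d | Imbalance | Rejection with no effect |
|---|---|---|---|
| 80% / 60% | 5 points | 1.0 | 5.6% |
| 90% / 50% | 10 points | 4.0 | 15.7% |
| 90% / 40% | 15 points | 7.5 | 42.5% |

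The formula itself depends on the assumed mechanism. If the comparison arm contains all the willing students plus others, the imbalance is (uptake gap ÷ comparison uptake) × d:

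- (0.20/0.80) × 5 = 1.25 points
- (0.40/0.90) × 10 = 4.4 points
- (0.50/0.90) × 15 = 8.3 points

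All these rates treat students as independent. With one school per arm, any variation between schools would move the rate away from 5% even without self-selection.

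**The case against.** The strongest reply is that an unspecified procedure is not a demonstrated bias. Much of that stands.

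- A reader might infer that students are enrolled after the roles are drawn. The article never says so. The inference rests on sentence order in a section that mixes tenses and describes the draw of schools after the allocation. The flowchart (Fig. 1) could not be seen for this review.
- A reader might infer that the EPaL arm is enriched with motivated families and the comparison arm is not. That is not supported. The seminar is not confined to one school, the criterion covers both, consent was taken in all cases, and comparison students could have EPaL materials later. Families there may also have been drawn in by EPaL.
- A reader might infer that an imbalance could never be detected. That goes too far. Stages of change for five behaviours, EAT-26 and healthy-lifestyle attitudes are measured at baseline in both schools, and would show it at least in part.
- The direction is open as well. Families worried about weight or eating might volunteer more readily.
- The article calls the design quasi-experimental and says that randomisation when recruiting participants would strengthen causal claims. This concedes that the groups may not be equivalent, though it does not name selective enrolment by arm.

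What the reply does not remove is the wording of the criterion. Even with the seminar in both schools, families who knew their school's role would be deciding on different commitments, and nothing in the text rules that out.

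**Conclusion.** The point holds as a risk, not as an established bias. The protocol ties eligibility to consent to the intervention and describes a single recruitment route that leads into EPaL. It gives no safeguard against families consenting with knowledge of their school's role. The arms may therefore differ in motivation through self-selection, which the listed limitation does not name and the tests named do not adjust for.

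Neither direction nor size can be derived from the document. The figure of about 16% rejection for a 4-point imbalance shows only how a moderate imbalance would act at 234 per arm. It rests on assumed uptake, an assumed difference between willing and unwilling students, 30% prevalence and no clustering. At the mild end of the assumed range (1 point, 5.6%) the effect is negligible.

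**What to change.** - **Criterion.** Replace consent to the intervention with consent to the study: the assessments, plus EPaL either now or after the final follow-up.
- **Recruitment.** State that the same seminar, with the same content, is held in both schools.
- **Sequence.** Draw the schools' roles, or at least disclose them, only after consent and baseline assessment are complete in both schools.

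The cost is a reordering of steps and a change to the consent sentence. Club timetabling and peer-educator training would start a few weeks later.

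Consent letters are described in the past tense and registration was retrospective, so recruitment may already be finished. In that case:

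- report eligible and consenting numbers by school;
- report the baseline profile by school, including stages of change and EAT-26;
- adjust the between-school comparison for these baseline values, recognising that this deals only with what was measured;
- limit the conclusion to students whose families opted in.

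None of these steps removes the confounding of school with arm, which follows from having one school in each.

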### Sample size calculation

The sample size calculation was based on the differences between groups (overweight and obese; and non-overweight and non-obese) in the proportion of having disordered eating. The value was taken from the outcome of needs assessment study, which was conducted involving 9677 adolescents aged 12–19 years throughout Malaysia. Based on the study, the proportion of overweight and obese adolescents who were having disordered eating was 40.3 %, whereas the proportion of non-overweight and non-obese adolescents who were having disordered eating was 27.9 %. Assuming a power of 80 % and a level of significance of 5 %, we needed 234 participants for each intervention and comparison groups, respectively. The effect size for proportions was estimated by the differences in the arcsine transformations of the respective proportions. The medium effect size of 25.4 % was obtained.

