## Background

Globalisation, urbanisation and economic development in the past century have had a negative impact on eating habits and exercise in both developed and developing nations. This impact is evident in modern adolescents’ eating and physical activity regimens. In Malaysia, adolescents, individuals aged 10–19 years, make up a population of 5.5 million i.e., 18.9 % of the entire Malaysian population [1].

At the age of adolescence, major physical, psychological and social changes occur. For instance, this stage of development is the second chance of catch-up growth before entering adulthood. Inadequate intake of carbohydrates, proteins, fat, vitamins and/or minerals has been shown to have severe consequences on growth during this stage, and is associated with delayed onset of puberty [2]. This is because nutritive demands of adolescence are only second to infancy. Excessive food intake, however, has also been shown to have detrimental effects on adolescents’ health, such as increasing their susceptibility to diseases and precipitating diabetes, heart disease and hypertension [3].

Overweight and obesity are major public health issues in both developed and developing countries. Between 1980 and 2013, the prevalence of overweight and obesity in developed countries remarkably increased from 16.9 and 16.2 % to 23.8 and 22.6 % in male and female adolescents respectively; whereas in developing countries, a whopping 9.8 % increase in the number of overweight and obese adolescents was observed around the same period of time [4].

In Malaysia, high percentages of overweight and obese adolescents, as well as adolescents suffering from disordered eating have been reported. According to the National Health and Morbidity Survey (NHMS), the prevalence of obesity in Malaysian adolescents increased dramatically between 2011 and 2015 from as low as 6.1 % [5] to 11.9 % [6]. Alarmingly, estimates from a separate nationwide study showed that as of 2015, 14.2 % of Malaysian adolescents aged 12–19 were overweight, while 10.1 % were rather obese [7].

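### The stated 80% power belongs to a survey contrast between weight-status groups, not to the comparison of the intervention and comparison schools

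*Protocol article*

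**What the plan says.** The Sample size calculation section of the protocol article says the number was "based on the differences between groups (overweight and obese; and non-overweight and non-obese) in the proportion of having disordered eating". The two rates come from a nationwide survey of 9677 adolescents aged 12–19: "The value was taken from the outcome of needs assessment study". In that survey "the proportion of overweight and obese adolescents who were having disordered eating was 40.3" %, and "the proportion of non-overweight and non-obese adolescents who were having disordered eating was 27.9" %. With 80% power "and a level of significance of 5" %, the section concludes that "we needed 234 participants for each intervention and comparison groups, respectively". It names the arcsine transformation as the effect-size method and adds: "The medium effect size of 25.4 % was obtained".

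The Study design and Setting, recruitment and participants sections define the arms differently. One school receives EPaL and another serves as the comparison. Students qualify by form (1 or 2), age (13–14) and parental consent; weight status is not a criterion.

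**The concern.** The two survey rates describe a cross-sectional association between weight status and disordered eating. Neither is an expected rate in a comparison school or in a school that has received EPaL. Both schools will contain students of every weight status, so neither arm resembles either survey group. The article gives no expected intervention effect and no argument for using the weight-status gap in its place.

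This is the only power statement in the article. A reader judging a result on disordered eating would take it that the study had 80% power for a between-school difference chosen in advance. No such difference was specified.

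**Working it through.** **Inputs from the article.** Rates 0.403 and 0.279; 80% power; 5% significance (two-sided taken, since one-sided gives only 180 per group); 234 per arm, 1:1. The Background section supplies "14.2 % of Malaysian adolescents aged 12–19 were overweight, while 10.1 % were rather obese", so 14.2% + 10.1% = 24.3% overweight or obese.

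**Step 1: reproduce the plan's figure.**

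- Effect size: h = 2·asin(√0.403) − 2·asin(√0.279) = 1.3756 − 1.1130 = 0.263.
- Arcsine formula: n = 2·((1.960 + 0.8416)/h)² = 2·(2.8016/0.2626)² = 227.7, so 228 per group.
- Pooled-variance formula for two proportions: 229 per group.
- Power at 234 per group for 40.3% versus 27.9%: 81%.

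The stated 234 is within 3% of both results. It is therefore the size for the weight-status contrast.

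**Step 2: check the reported effect size.** The article's own method gives 0.263, not 0.254. Using 0.254, n = 2·(2.8016/0.254)² = 243.3, so 244 per group. The reported effect size thus fits neither its inputs nor the 234. The consequence is small: at h = 0.254, 234 per group still has about 78% power.

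**Step 3: assume a baseline for a mixed school.** The article gives no expected rate for either arm. If a school resembles the survey population, prevalence is 0.243 × 0.403 + 0.757 × 0.279 = 0.309. This is an assumption for illustration.

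**Step 4: individual-level power between arms with 234 each.** Power = Φ[(d − 1.960·SE₀)/SE₁], where d is the difference, SE₀ uses the pooled proportion and SE₁ the separate proportions. For a 10-point fall (30.9% to 20.9%), SE₀ = 0.0405 and SE₁ = 0.0402, so power = Φ[(0.100 − 0.0794)/0.0402] = Φ(0.51) = 70%.

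| Fall from 30.9% | Power with 234 per arm | n per arm for 80% |
|---|---|---|
| 5 points | 22% | 1276 |
| 8 points | 50% | 482 |
| 10 points | 70% | 301 |
| 12.4 points | 88% | 189 |

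Power reaches 80% at a fall of about 11.3 points, to 19.6%, a relative reduction of about 37%.

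**Step 5: one further scenario.** Suppose EPaL brought overweight and obese students down to 27.9% and changed nobody else. The arms would then differ by 30.9 − 27.9 = 3.0 points, and power would be about 11%. If 20% to 35% of students are overweight or obese, power runs from 9% to 17%.

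**The case against.** The strongest reply is that the calculation is numerically sound and that h is a standardised effect. With 234 per arm, individual-level power is about 80% for any between-arm difference with h near 0.26, whatever produced that value. Carried over to a 30.9% baseline, the planning effect gives about 81% power as the same h, 88% as the same 12.4-point gap, and 65% as the same relative fall (27.9/40.3, about 31%). This stands as far as it goes: the number is not a miscalculation, and the study is not shown to be badly sized. It does not answer the point, because the article never says that an effect of this size is expected between schools.

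A reader might infer from Step 5 that the trial has only about 11% power, or that it was never sized for a plausible effect. The article supports neither reading. EPaL is described as universal prevention, aimed at disordered eating among adolescents generally, so nothing justifies assuming no effect in students who are not overweight. Because no between-arm effect is stated, none can be called implausible. The 11% is one scenario among several.

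The effect-size discrepancy is rightly called minor: about 3%, with little effect on power. A condensed article may also omit a rationale held in a fuller protocol, but the paragraph as printed ties the 80% to the wrong groups and needs correcting in either case.

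**Conclusion.** The point holds. The 234 per arm and its 80% power are derived from a difference between weight-status groups in a survey, while the trial compares two schools of mixed weight status. The fault lies in the choice of contrast, not in the arithmetic.

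No single corrected power can be given. For falls of 5 to 12.4 points it ranges from 22% to 88%, assuming a baseline of about 30.9%, a two-sided 5% test and independent students. The independence assumption is favourable to the trial: with one school per arm and some loss to follow-up, true power is lower than these figures. The misreported effect size is a secondary slip.

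**What to change.** Rewrite the sample-size paragraph as follows:

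- Remove the statement that the size derives from 40.3% versus 27.9%.
- State what 234 per arm can detect between arms, with its baseline. For example: assuming a comparison-school prevalence of about 31%, 234 students per arm give 80% individual-level power for a fall of about 11 points, to about 20%. Ideally give the range in Step 4 as well.
- Say plainly that this figure takes no account of allocation by school, with one school per arm, or of loss to follow-up, so true power is lower.
- If the investigators have a reason to expect a between-school effect of this size, state it. If not, say that the detectable difference was worked out from the fixed sample size.
- Correct the effect size to h = 0.263, or delete the sentence, including the word medium.

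The cost is wording only. Enrolment, assessments and analysis are unchanged, but the power statement becomes less favourable.

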### Data analysis

Data will be analysed by using version 21 of the IBM SPSS Statistical software (IBM SPSS Statistics, Inc., Chicago, IL, USA). Depending on the distribution of the variable of interest, descriptive statistics of continuous data will be presented by using the mean and standard deviation, and the median and the inter-quartile range. Categorical data will be presented as frequencies and percentages. *T*-test will be used to detect differences between groups for continuous variables, while chi-square will be used to investigate possible correlations between categorical variables. The repeated measures analysis of variance (ANOVA) will be used to detect significant differences within the groups. The evaluation of the intervention will be based on an intention-to-treat analysis. Differences with *p*-values < 0.05 were considered significant.

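### On its own inputs the 234 per group holds at most about a 2.6% margin for loss, and none at the printed effect size, so the stated 80% power depends on near-complete follow-up

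*Protocol article*

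**What the plan says.** The Sample size calculation section of the protocol article gives all its numerical inputs. From a national survey, "the proportion of overweight and obese adolescents who were having disordered eating was 40.3" per cent and "the proportion of non-overweight and non-obese adolescents who were having disordered eating was 27.9" per cent. The error rates are given as "Assuming a power of 80" per cent and "a level of significance of 5" per cent. The effect size is the difference of arcsine-transformed proportions, printed as 25.4%. The conclusion is that "we needed 234 participants for each intervention and comparison groups, respectively". The section describes no step for loss to follow-up, and the text gives no larger recruitment target.

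The Setting, recruitment and participants section puts the assessments "prior to the intervention (baseline), after the final session of the programme (post-intervention) and 3 months thereafter (follow-up"). The programme itself lasts 16 weeks. The Disordered eating section makes that outcome a cut-off on a self-completed questionnaire score (EAT-26). The Data analysis section states that "The evaluation of the intervention will be based on an intention-to-treat analysis", and that "Differences with *p*-values < 0.05 were considered significant".

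**The concern.** The article presents 234 per group as the number that gives 80% power. A reader will take the 80% as applying to the comparison that answers the trial's question, and that comparison is made after baseline: about 16 weeks in, and again 3 months later. A student who is absent or has withdrawn at that visit has no EAT-26 score. Intention-to-treat settles which school a student is counted in, but it does not supply a missing score.

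If 234 is close to the bare analysable number, the 80% survives only with almost complete data at those visits. What is at stake is how a null result is read: it could be reported as coming from an 80%-powered comparison when fewer students were analysed than that figure needs. The printed effect size raises a second doubt, because it does not match the printed proportions and asks for more than 234.

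**Working it through.** **Inputs** (Sample size calculation section): p1 = 0.403, p2 = 0.279, power 0.80, alpha 0.05, equal groups, arcsine effect size, printed effect size 0.254, stated n = 234 per group. Sidedness is not stated. I read it as two-sided, in line with the p < 0.05 rule and the t-test and chi-square test in the Data analysis section. Loss to follow-up is not stated; 5% to 20% below is my assumption.

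**Step 1. Effect size from the printed proportions.**
h = 2·asin(√0.403) − 2·asin(√0.279) = 0.2626. The article prints 0.254.

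**Step 2. Reproduce the sample size.**
n = 2·(1.960 + 0.842)² / h².
- With h = 0.2626: n = 227.7, so 228 per group.
- With h = 0.254: n = 243.3, so 244 per group.
- As a check, the pooled two-proportion formula gives 229 and the continuity-corrected formula 245.

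The arcsine and pooled results from the printed proportions are within 3% of the stated 234, and neither contains a dropout term. Working backwards, n = 234 corresponds to h = 0.2590, which is neither the effect the proportions give nor the one printed.

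**Step 3. Margin in 234.**
234 − 228 = 6 students, and 6/234 = 2.6%. By the pooled formula it is 234 − 229 = 5. At the printed effect size there is no margin, since 234 is 10 below 244.

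**Step 4. Power by number analysed per school.**
Power = Φ(h·√(n/2) − 1.960). The losses are counted from 234 enrolled.

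| Assumed loss | Analysed per school | Power, h = 0.2626 | Power, h = 0.254 |
|---|---|---|---|
| none | 234 | 81.1% | 78.4% |
| 2.6% | 228 | 80.1% | 77.4% |
| 3.0% | 227 | 79.9% | 77.2% |
| 5% | 222 | 79.0% | – |
| 10% | 211 | 76.9% | 74.2% |
| 15% | 199 | 74.5% | – |
| 20% | 187 | 71.9% | 69.0% |

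On the printed proportions, the seventh missing student in each school takes the power below 80%. On the printed effect size it starts below 80%.

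**The case against.** The strongest reply is that 234 is stated as a requirement. The article nowhere calls it the enrolment target or a cap. The eligibility rule sets no ceiling, the flowchart in Fig. 1 is not shown, and a condensed article may leave recruitment numbers to the full protocol. If 234 is the analysable number and more are enrolled, the printed proportions support it, at 81.1%. This stands: a reader might infer that exactly 234 students per school are enrolled with no allowance for loss, and the article does not say so. It does not remove the point. The text offers no other number, and even as an analysable number 234 does not reach 80% at the effect size printed beside it.

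The route to 234 is also unknown. A one-sided test would need 180 per group, and 180 × 1.3 = 234. One-sided power at 234 is 88.4%, and still 81.4% with 187 analysed. So the margin of 6 depends on the two-sided reading. But the article states neither a one-sided test nor a 30% allowance, and its p < 0.05 rule is naturally read as two-sided.

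A reader might further infer that the trial will miss 80% power. The documents do not support that: they give no loss rate, sessions run in school during co-curriculum periods, and at 5% loss the shortfall is only one point.

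Finally, the 80% is weak for larger reasons. The two proportions compare weight-status groups, not intervention with comparison, and the formula treats students as independent although there is one school per arm. This also stands. It means that the recomputed powers should be labelled nominal, and that restating them must not be taken as endorsing the calculation.

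**Conclusion.** The point holds in conditional form. On the printed proportions, two-sided and by the arcsine method, about 228 analysed students per group are needed, so 234 contains at most about a 2.6% margin. At the printed effect size of 25.4% there is no margin, and power is 78.4% with complete data. If 234 is the number enrolled, the stated 80% is lost at the post-intervention or 3-month assessment once more than about 6 students per school lack disordered-eating data.

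The shortfall is small at 5% loss (about 1 point) and about 3 to 8 points at 10% to 20%. Those loss rates are assumptions. The conclusion also rests on the two-sided reading and on 234 being the number enrolled. All the powers quoted are nominal. The mismatch between 0.254 and 0.263 needs no assumption about loss: it follows from the printed proportions alone.

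**What to change.** Keep the enrolment and restate the figure in the sample size section:

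- Say whether 234 is the number enrolled or the number analysed.
- Say that the 80% is nominal, applies to about 228 students per school with disordered-eating data at the assessment being tested, and treats students as independent.
- Correct the effect size to 0.263, or keep 0.254 and restate the power for it (78.4% at 234).
- Give the power at the expected loss, for example about 77% at 10% and 72% at 20% on the printed proportions.
- In the report, give confidence intervals from the number analysed at each visit, and do not describe a null result as coming from an 80%-powered comparison.

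The cost is a few sentences and a slightly less favourable stated power. No extra students and no change of design are needed.
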